### Eligibility criteria

Patients who were successfully treated with (chemo)radiotherapy for squamous cell carcinoma of the oropharynx >2 years ago and have grade 2 or 3 xerostomia after radiotherapy according to the Common Terminology Criteria for Adverse Events (CTCAE) v.5.0 scale will participate in the study.^24^ Inclusion and exclusion criteria will be used to determine whether they can be included in the study (Table 2).

**TABLE 2. j_raon-2023-0052_tab_002:** Inclusion and exclusion criteria

**Inclusion criteria**	**Exclusion criteria**
Squamous cell carcinoma of the oropharynx, UICC TNM (8^th^ ed.) stage cT1–2N+ or cT3–4cN0–3 M0, treated with curative intent RT (TD 66–70 Gy, bilateral neck irradiation) with or without concurrent chemotherapy	Newly diagnosed malignant tumor anywhere in the body within the last two years
Two years or more after treatment with no evidence of locoregional recurrence or systemic metastasis	Active smoker
Nonsmoker or former smoker (quit smoking ≥ 2 years ago)	Use of xerogenic medications (e.g., tricyclic antidepressants, antipsychotics, decongestants, bronchodilators, antihypertensive agents such as beta blockers and diuretics, antihistamines, hypnotic sedatives, opioids, and muscle relaxants)
Mean radiation dose > 26 Gy to each of the parotid glands and > 35 Gy to each of the submandibular glands	Other salivary gland disorders (e.g., Sjoegren's syndrome, scleroderma, sialolithiasis, etc.)
Grade 2 or 3 xerostomia as assessed by the CTCAE v5.0 scale	Patients receiving anticoagulant therapy that cannot be discontinued during the procedure
Clinically decreased salivation and hyposalivation (unstimulated total salivary flow of 0.05–0.20 ml/min)	Pregnancy or planned pregnancy within the next two years
Age between 18–75 years	Breastfeeding
Both sexes	Active, uncontrolled infection
Signed “Informed Consent Form” to participate in the study	Other medical (including psychiatric) conditions that, in the opinion of the investigators, preclude safe administration of the planned therapy and completion of follow-up visits
	Known substance abuse or alcoholism

CTCAE v.5 = Common Terminology Criteria for Adverse Events version 5.0; RT = radiotherapy: TD = tumor doses; UICC = *Union for International Cancer Control*

Criteria for subsequent exclusion of patients from the study are: pregnancy, infection at the graft site, allergy to local anesthetics or citric acid, and withdrawal of consent to participate in the study.

If a patient is excluded from the study prior to evaluation of the effect of the intervention under study, she or he will be replaced by another patient, leaving the final number of included patients at 10.

### Inclusion of patients

Candidates for inclusion in the study will be selected from patients who are regularly monitored in the follow-up clinics for patients with head and neck cancer at the Institute of Oncology Ljubljana. Patients who meet the basic inclusion criteria will be informed about the study and invited to participate. The study will not be randomized.

### Pre- and post-treatment assessment

After being informed about participation in the study and signing the Informed Consent form, patients will undergo the following tests and complete the following questionnaires during the 4-week period before MSC application, i.e., the procedure (Table 3). The same measurements will be performed and questionnaires completed at both the 4-week and 4-month follow-up, with the exception of core needle biopsy and salivary gland scintigraphy (these will be repeated only at the 4-month follow-up). All procedures in the study are listed in Table 3.

**TABLE 3. j_raon-2023-0052_tab_003:** Procedures of the study

**Procedures**	**Inclusion**	**Intervention**	**Follow-up examinations**			

	**W4→0**	**D0**	**D1**	**D5**	**D28**	**D120**
Patient screening with clinical and objective evaluation of xerostomia^1^	X					
Complete blood count, biochemistry	X				X	X
Coagulation profile	X					
Measurement of unstimulated and stimulated salivary flow rate	X				X	X
Determination of salivary composition	X				X	X
Magnetic resonance imaging	X				X	X
US elastography	X				X	X
Scintigraphy with [99mTc]Tc-HMPAO labeled MSCs		X				
Scintigraphy with (*[99mTc]TcO_4_^−^*)	X					X
Core needle biopsy of the gland^2^	X					X
Visual Analog Scale questionnaire	X				X	X
Xerostomia Questionnaire	X				X	X
EORTC QLQ-H&N35	X				X	X
Toxicity assessment, CTCAE v.5		X	X	X	X	X

CTCAE v.5 = Common Terminology Criteria for Adverse Events version 5.0; D = day; EORTC QLQ-H&N35 = European Organisation for Research and Treatment of Cancer Quality of Life Questionnaire Head and Neck Module; MSCs = allogeneic mesenchymal stromal stem cells; US = ultrasound; W = week; [99mTc]*HMPAO = T*echnetium 99m-hexamethylpropyleneamine oxime; *[99mTc]TcO_4_^−^* = *T*echnetium 99m-pertechnetate

1 Inclusion criteria, see Table 2.

2 From the parotid gland: the first 5 patients included in the study; from the submandibular gland: the last 5 patients included. The gland on the side that received a higher dose of radiation will be punctured.

The study also involves 10 volunteers (control group) who do not participate in the procedure. They will sign the Informed Consent to Participate in the Study and provide saliva samples for the measurement of unstimulated and stimulated salivary flow and for the determination of salivary composition (for comparison with the intervention group).

#### Measurement of unstimulated total salivary flow rate

Patients will be instructed to drink at least 2 liters of fluid the day before saliva sample delivery and to abstain from food, drink, and oral hygiene for at least 1 hour before. After a 5-minute break, they will rinse the mouth with a sip (15–20 ml) of cold water from the refrigerator. Unstimulated saliva will be collected for 10 minutes in a pre-weighed disposable plastic container. Saliva samples will be frozen in liquid nitrogen 15 minutes after collection and stored at −80°C for further analysis. Saliva collection will take place between 10:00 and 12:00 in the same room and in the presence of the same physician, before the procedure, 4 weeks and 4 months after the procedure. The flow rate will be calculated assuming that 1 g of saliva is equivalent to 1 ml.^25^

#### Measurement of stimulated total salivary flow rate

The procedures before and after saliva collection will be the same as those for measuring unstimulated saliva. After a 5-min break, patients will chew tasteless kerosene wax for 1 min and rinse the mouth with a sip (15–20 ml) of cold water from the refrigerator. Stimulated saliva collection (while chewing the wax) will be performed for 5 minutes in a disposable plastic container, before the procedure, at 4 weeks, and at 4 months after the procedure.

#### Analysis of the composition of unstimulated and stimulated saliva samples

Several characteristics or components will be determined in the saliva samples:
pH measurement (SevenCompact™ pH meter S210 with the electrode InLab Micro Pro-ISM, Mettler Toledo, Columbus, Ohio);total protein concentration, spectrophotometry at 280 nm (NanoDrop One, ThermoFisher Scientific Inc., Waltham, MA, USA);α-amylase activity, spectrophotometry at 405 nm (GENESYS™ 150 Vis/UV, ThermoFisher Scientific Inc., Waltham, MA, USA);concentration of mucins (MUC1), ELISA (ThermoFisher Scientific Inc., Waltham, MA, USA);total esterase activity, spectrophotometry at 270 nm (GENESYS™ 150 Vis/UV, ThermoFisher Scientific Inc., Waltham, MA, USA)^26^;paraoxonase activity, spectrophotometry at 405 nm (GENESYS™ 150 Vis/UV, ThermoFisher Scientific Inc, Waltham, MA, USA).^27,28^

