**Secondary**		
Efficacy of the procedure	Measurement of unstimulated/stimulated salivary flow and saliva composition	During recruitment, day 28 and 120 post-procedure
	Assessment of subjective degree of xerostomia (questionnaires)	During recruitment, days 28 and 120 after the procedure
		Immediately after the procedure (day 0)
	Scintigraphic evaluation of grafting, retention, and migration of allogeneic MSCs	During recruitment, on days 28 and 120 after the procedure
	Assessment of patients’ quality of life	
Radiological changes of the salivary tissue	Magnetic resonance imaging (MRI): volume, signal, and diffusivity changes	During recruitment, on days 28 and 120 after procedure
	Ultrasonography (US): consistency (firmness)	
Functional changes of the salivary tissue	Scintigraphy with ([99mTc]TcO_4_^−^ (pertechnetate): uptake of radioisotope in parenchyma, ejection fraction	During recruitment, on days 28 and 120 after procedure
Morphological changes of the salivary tissue	Core needle biopsy specimens: composition, inflammatory infiltrate, metaplasia, reactive changes	During recruitment, on day 120 after the procedure

CTCAE v.5 = Common Terminology Criteria for Adverse Events version 5.0; MSCs = allogeneic mesenchymal stromal stem cells

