### Statistical methods

Since this is an exploratory study, no formal sample size calculation was performed.

Data will be managed in databases with Excel spreadsheets and analyzed with statistical analysis software such as SPSS, GraphPad Prism, or similar tools. Changes in absolute values and percent deviations from baseline salivary flow rate values before and after the procedure will be analyzed and compared at different time points within the intervention group; baseline values will also be compared with those of the control group. Numeric variables will be compared with paired t tests or nonparametric tests if the assumptions for parametric tests are not met.

The scores of the individual items of the VAS questionnaire and the Xerostomia questionnaire will be summed, and the total score is linearly transformed into a scale from 0 to 100.^29,30^ Scoring and interpretation of the EORTC QLQ-H&N35 questionnaire will be performed according to EORTC guidelines.^31^

Comparisons of MRI, ultrasound, scintigraphy, and analysis of core-needle biopsies taken before and after procedure will be descriptive in nature.

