In addition, Lynggaard *et al*. published encouraging results on the treatment of radiation-induced xerostomia with allogeneic adipose-derived MSCs.^39^ The use of allogeneic MSCs offers numerous logistical advantages: surgical intervention is no longer required to obtain the starting material, and the quality of the final preparations can be better controlled.^40^ In this study, 25×10^6^ MSCs were inserted into each submandibular gland and 50×10^6^ MSCs were inserted into each parotid gland in ten patients; the follow-up period was four months. During this period, an increase in mean unstimulated salivary flow was measured from an initial 0.13 ml/min to 0.18 ml/min. Stimulated salivary flow also increased after therapy from 0.66 ml/min to 0.75 ml/min. Patients’ subjective perception of an improvement in xerostomia was confirmed by questionnaire results, and no serious adverse events were reported during the study period.^39^

Recently, a dose-escalating phase I study protocol (3 + 3 design) was published for the treatment of radiation-induced xerostomia in patients with head and neck cancer with interferon-gamma-stimulated autologous bone marrow stromal cells.^41^ The results of this study are not yet available. However, in a pilot study, the same group has already used MSC prepared in this manner in six patients who received a single injection of 10×10^6^ MSC into a single mandibular salivary gland and found that the therapy was well tolerated and showed a trend toward improvement in salivary volume and quality of life.^42^

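### Saliva protein and MUC1 are efficacy measures defined as concentrations, with no output per minute beside them, so dilution cannot be told from changed secretion when flow changes

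*Protocol article*

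**What the plan says.** Table 1 of the protocol article (Objectives) gives the efficacy measure as "Measurement of unstimulated/stimulated salivary flow and saliva composition", assessed at recruitment and on days 28 and 120.

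The section on analysis of saliva composition lists six items for unstimulated and stimulated samples. One is pH. Two are explicitly amounts per volume: "total protein concentration, spectrophotometry at 280 nm" and "concentration of mucins (MUC1), ELISA". Three are activities without a unit or denominator: "α-amylase activity, spectrophotometry at 405 nm", total esterase and paraoxonase.

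Statistical methods describes a change measure for flow only: "Changes in absolute values and percent deviations from baseline salivary flow rate values before and after the procedure will be analyzed". Composition comes under the general rule, "Numeric variables will be compared with paired t tests", with nonparametric tests as the fallback. No output per minute or flow-adjusted variable is named.

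Healthy volunteers also give saliva, among other things "for the determination of salivary composition (for comparison with the intervention group". They are sampled once.

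**The concern.** The amount of a component secreted per minute is its concentration times the flow. If treatment raises flow, concentration can fall, hold or rise depending on what happens to output, and the concentration alone does not show which.

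The Discussion supports the approach with animal data on mucin secretion and amylase production. Those are statements about amount produced, and a concentration does not measure amount when flow is changing. Two misreadings are possible. A treatment that raises only the fluid could look like a loss of secretory product. A real gain in output could be hidden, or could appear as a decline.

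**Working it through.** The article gives no figure on this point to reproduce, and states no alpha, SD or effect size. The check is dilution arithmetic on flows that the article cites.

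**Inputs (Discussion, cited studies)**
- Allogeneic study at the same cell numbers per gland: "an increase in mean unstimulated salivary flow was measured from an initial 0.13 ml/min to 0.18 ml/min"; stimulated flow went from 0.66 to 0.75 ml/min.
- Placebo-controlled trial of autologous cells: unstimulated flow gains of 33% at one month and 50% at four months.

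**Formula**

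Output per minute = concentration × flow. Therefore concentration ratio = output ratio ÷ flow ratio.

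**Flow ratios**
- Unstimulated: 0.18 / 0.13 = 1.385
- Stimulated: 0.75 / 0.66 = 1.136

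**Change in concentration, allogeneic study flows**

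| True change in output | Unstimulated | Stimulated |
|---|---|---|
| None (constant output) | 1/1.385 − 1 = −27.8% | 1/1.136 − 1 = −12.0% |
| +20% | 1.2/1.385 − 1 = −13.3% | 1.2/1.136 − 1 = +5.6% |
| In proportion to flow | 0% (output +38.5%) | 0% (output +13.6%) |

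With the placebo-controlled trial's flow gains and constant output, the falls are 1/1.33 − 1 = −24.8% and 1/1.5 − 1 = −33.3%.

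**Could pure dilution reach significance with ten patients?** This is an illustration only. It assumes a paired t test on the log scale, two-sided 0.05, n = 10, and an assumed SD of the log change.

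| Assumed SD | 0.2 | 0.3 | 0.4 | 0.6 | 0.8 |
|---|---|---|---|---|---|
| Unstimulated | 99.5% | 86.2% | 63.1% | 33.5% | 21.1% |
| Stimulated | 43.9% | 22.6% | 14.8% | 9.3% | 7.4% |

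**How many comparisons are exposed**
- All before-after composition comparisons: 6 items × 2 sample types × 2 follow-up visits = 24.
- Certain (protein, MUC1): 2 × 2 × 2 = 8.
- If the three activities are also per ml: 5 × 2 × 2 = 20. If they are expressed per mg protein, dilution cancels and they drop out.

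**Volunteers.** Patients must have unstimulated flow of 0.05–0.20 ml/min (Table 2). If the volunteers' flow is higher, a difference in concentration mixes flow with secretion in the same way.

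**The case against.** The strongest reply is that the composition section is an assay list and does not define analysis variables. The rule on numeric variables would cover a derived output equally well, and a condensed article may leave derived variables to a full protocol or analysis plan that is not shown. This stands in part: a reader might infer that composition will be compared only on the concentration scale, and the article does not say so. However, the article does give derived measures for flow and for the questionnaires, and for protein and MUC1 the only quantity it names is a concentration.

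Four further limits stand.
- A reader might infer that all five analytes are measured per volume. The article gives no unit for the three activities, so only protein and MUC1 are certain.
- A reader might take the 27.8% and 12.0% falls as predictions. They are the constant-output bound. The article expects gland regeneration, in which case output may rise with flow. The flows are also group means from a different cell product.
- A reader might suppose that volunteer flow differs by design. No flow criterion is given for volunteers. Higher flow is likely but not stated, and this comparison does not estimate the treatment effect.
- A reader might conclude that output should replace concentration. The stated objective is composition, and concentration describes that directly. The Introduction also treats lack of saliva and altered saliva as distinct causes of dry mouth.

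**Conclusion.** The point holds in a limited form. Protein and MUC1 are efficacy measures defined as concentrations, for a treatment intended to change flow, and no measure is named that separates dilution from secretion. At the flow changes the article cites, the ambiguity runs from a 27.8% fall to no change in unstimulated saliva, and from a 12.0% fall to no change in stimulated saliva. This assumes that true output lies between constant and proportional to flow. It affects 8 of 24 before-after comparisons for certain and at most 20.

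The severity is minor. Composition is one part of a secondary objective in an exploratory phase I study whose primary objective is safety, and no decision rule or direction of benefit is attached to any component. The documents do not support the stronger conclusion that the composition analysis is wrong or that it will show a spurious decline.

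**What to change.** In Statistical methods:
1. State the units of the amylase, esterase and paraoxonase activities.
2. For protein, MUC1 and any activity expressed per ml, analyse output per minute (concentration or activity per ml × flow in ml/min from the same collection) beside concentration. Do this separately for unstimulated and stimulated saliva, in both the before-after and the volunteer comparisons.
3. State that a fall in concentration will not be read as lost secretion unless output also falls.

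The cost is two or three sentences. Flow is already measured at the same collections, so no new samples, assays or visits are needed. Fixing this before results are seen also avoids choosing the more favourable scale afterwards.

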#### Contrast-enhanced magnetic resonance imaging (MRI) of the neck

MRI scans will be performed before, 4 weeks, and 4 months after MSC application using a 1.5T General Electric Optima 450W scanner. The protocol will include T1 FSE sequences in the axial plane, T2 PROPELLER sequences, diffusion weighted sequences (b=0, b=400, b=800) with calculation of ADC maps and 3D T1 SPGR sequences. Volumetric analysis of salivary glands using AW server software, signal changes and diffusivity analysis will be performed.

#### Ultrasonographic examination of the salivary glands

Ultrasonography elastography (UE) will be performed before, 4 weeks, and 4 months after MSC application to assess the consistency (firmness) of the parotid and submandibular glands. Measurements will be taken using the Hitachi Arrieta 850 device immediately prior to ultrasound-guided biopsy of one of the glands.

#### Scintigraphy with [99mTc]Tc-HMPAO-labeled MSCs.

One hour and twenty-four hours (the next day) after MSC application, planar head and whole-body images and SPECT/CT images of the head will be performed to assess the distribution, retention, and migration of MSCs from the application site.

#### Scintigraphy with *[99mTc]TcO_4_^−^*

Before and 4 months after MSC transplantation, scintigraphy of the salivary glands will be performed with the radiopharmaceutical pertechnetate (*[99mTc]TcO_4_^−^*). After intravenous administration, the radiopharmaceutical accumulates in the functioning parenchyma of the salivary glands and is subsequently excreted into the oral cavity after stimulation with citric acid. After administration of the radiopharmaceutical, a 10-minute planar head recording will be made, followed by oral administration and stimulation of the salivary glands with citric acid and another 10-minute planar recording. In this study, the uptake of the radiopharmaceutical in the functioning parenchyma and the excretory fraction of each gland will be evaluated qualitatively and semiquantitatively. Both parameters, determined before and after MSC transplantation will be compared.

#### Percutaneous core needle biopsy of the salivary gland.

A sample will be taken from the parotid gland in the first 5 patients enrolled in the study, while a sample will be taken from the submandibular gland in the last 5 patients. The gland on the side of the head or neck that received a higher dose of radiation during RT will be punctured. The biopsy will be performed in each patient before the procedure and 4 months after, both times from the same gland.

The biopsy will be performed under local anesthesia and ultrasound guidance. Before the procedure, blood coagulation parameters will be determined (platelet count, prothrombin time, international normalized ratio). Patients taking anticoagulant medications will be instructed to discontinue them one week prior to the procedure.

Tissue samples stained with hematoxylin and eosin will be examined by a pathologist. For both pre- and post-procedure specimens, the pathologist will semi-quantitatively evaluate and compare the percentage of serous, mucinous, and mixed acini, ducts, adipose tissue, and fibrosis in the specimen. The pathologist will also evaluate the presence, amount, and composition of the inflammatory infiltrate, possible metaplasia (e.g., squamous or oncocytosis), and reactive changes such as hyperplasia, atrophy, and signs of regeneration. Any other pathologic findings will also be described. If necessary and if sufficient tissue will be available, additional special and immunohistochemical staining will be performed.

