## Methods and design

The study is being conducted at the Institute of Oncology Ljubljana in collaboration with the Slovenian Institute for Transfusion Medicine, the Clinic of Nuclear Medicine at the University Medical Centre Ljubljana, and the Institute of Biochemistry and Molecular Genetics at the Faculty of Medicine, University of Ljubljana. It is a non-randomized, single-center, open-label, phase I exploratory study. The study will include 10 patients (intervention group) and 10 healthy volunteers (control group) (Figure 1).

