**FIGURE 1. j_raon-2023-0052_fig_001:**
[figure not shown]
Design of the clinical trial. CTCAE v5 = Common Terminology Criteria for Adverse Events version 5.0; MRI = magnetic resonance imaging; MSC = allogeneic mesenchymal stromal stem cells; RT = radiotherapy; SCC = squamous cell carcinoma; US = ultrasound; [99mTc]*HMPAO* = Technetium 99m-hexamethylpropyleneamine oxime; [99mTc]TcO_4_ = Technetium 99m-pertechnetate

The aim of the study is to evaluate the safety and preliminary efficacy of treatment of xerostomia after irradiation with allogeneic MSC from umbilical cord tissue. Thus, we hypothesize that the treatment of post-radiation xerostomia with allogeneic MSC from umbilical cord tissue is safe and effective.

The study protocol was approved by the National Medical Ethics Committee (No. 0120-193/2023/3) and registered in the ClinicalTrial.gov database (NCT06012604) under the title: “*Treatment of Post-radiation Xerostomia with Allogeneic Mesenchymal Stromal Stem Cells: A Pilot Study”,* registered on 22 August 2023; https://classic.clinicaltrials.gov/ct2/show/NCT06012604

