### Objectives

The primary objective of the study is to evaluate the safety of administering allogeneic MSCs to the submandibular and parotid glands of patients with radiation-induced salivary gland dysfunction and xerostomia, with a 4-month follow-up after the procedure.

Secondary objectives of the study include evaluation of the efficacy of the procedure and radiologic, functional, and morphologic changes in glandular tissue after application of allogeneic MSC (Table 1).

**TABLE 1. j_raon-2023-0052_tab_001:** Primary and secondary objectives of the study

**Objective**	**Definition of objective**	**Time of evaluation**

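### No masking to visit is described for the judgement-based before/after reads of biopsies and pertechnetate scans, so reader expectation could shift these secondary results

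*Protocol article*

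**What the plan says.** The Methods and design section describes the study thus: "It is a non-randomized, single-center, open-label, phase I exploratory study". The aim, given with Figure 1, names the expected direction: "we hypothesize that the treatment of post-radiation xerostomia with allogeneic MSC from umbilical cord tissue is safe and effective". The Conclusions add that the therapy is expected to regenerate glandular tissue.

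The secondary objectives include "evaluation of the efficacy of the procedure and radiologic, functional, and morphologic changes in glandular tissue". Three of the methods behind them matter here:

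- **Histology.** One gland per patient is biopsied at baseline and at 4 months: the parotid in the first 5 patients, the submandibular in the last 5. The reading of each pair is described as follows: "the pathologist will semi-quantitatively evaluate and compare the percentage of serous, mucinous, and mixed acini, ducts, adipose tissue, and fibrosis in the specimen". Inflammation, metaplasia, and reactive changes that include atrophy and evidence of regeneration are judged as well.
- **Pertechnetate scintigraphy.** Uptake and excretory fraction of each gland "will be evaluated qualitatively and semiquantitatively", and the values before and after are compared.
- **MRI.** "Volumetric analysis of salivary glands using AW server software, signal changes and diffusivity analysis will be performed".

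The Statistical methods section makes the comparisons of biopsy, scintigraphy, MRI and ultrasound descriptive. According to the Abstract, the control group contributes only salivary flow and composition.

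**The concern.** A semi-quantitative percentage of acini or fibrosis, a judgement on whether a gland shows regeneration, and a qualitative read of a scan all leave the reader room to lean one way. If the reader knows which specimen or scan came after treatment, and the treatment is expected to regenerate the gland, the lean is likely to favour improvement. In an open-label study, a reader will usually know the visit unless someone takes a step to hide it. The article describes no such step.

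At stake is how far the morphological and functional results can be believed. The Discussion says that the study's results will inform the design of later trials, and that the nuclear medicine studies should further define the treatment effect and make comparison with other work more credible. A before/after change that may partly reflect the reader serves those purposes poorly.

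**Working it through.** The article gives no reader variability, effect size or standard deviation for histology or imaging, and no sample-size calculation ("Since this is an exploratory study, no formal sample size calculation was performed"). There is no stated figure to reproduce. The check is to set the sections side by side and follow how a reader's tilt would travel.

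**1. How a tilt enters the result.** Write each score as the true value plus the reader's tilt at that visit:

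observed change = (true post + tilt post) − (true pre + tilt pre) = true change + (tilt post − tilt pre)

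A tilt that is the same at both visits cancels. A tilt that depends on knowing the visit does not cancel, and it stays in the change in full.

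**2. Whether anything in the design removes it.**

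- *A comparator.* With control tissue or images read by the same person in the same way, a shared tilt would subtract out. The controls give saliva only, so there is nothing to subtract.
- *Numbers.* There are 5 parotid and 5 submandibular biopsy pairs, 5 + 5 = 10 pairs or 20 specimens. A systematic tilt would not average out with more patients in any case. With 5 pairs per gland type it is also hard to recognise.
- *Coding.* The Confidentiality section identifies patients by code. That hides who the patient is, not which visit the material came from.
- *Masking or reading order.* Neither is mentioned in the biopsy, scintigraphy, MRI, course-of-study or statistical sections.
- *Descriptive analysis.* This avoids a false claim of significance. It does not remove the tilt, because the reader's score is itself the reported result.

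**3. Which reads are exposed.**

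| Outcome | Nature of the read | Exposed? |
|---|---|---|
| Biopsy before and at 4 months | Semi-quantitative percentages and judged reactive changes | Yes |
| Pertechnetate scan before and after | Partly qualitative, partly semi-quantitative | Yes, mainly the qualitative part |
| MRI volume and diffusivity | Software volumetry and calculated ADC maps; manual input not stated | Cannot be shown |
| MRI signal changes | Method of assessment not stated | Only if judged by eye |
| Scan of labelled cells | Taken only after the procedure | No before/after contrast |
| Ultrasound elastography | Measured live at the visit | Reading cannot readily be masked later |

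**4. Whether masked reading is feasible.** Stained slides and scintigraphy files can be kept and read later. An open-label treatment does not require an open reading. When the visit is hidden and the order is random, the part of (tilt post − tilt pre) that comes from knowing the visit has expectation zero.

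**The case against.** The strongest objection is that the point rests on silence. A reader might infer from the open-label label and the before/after wording that the pathologist and the scintigraphy reader know the visit. The article does not say so. Two specimens can be compared without knowing which came first, and a journal article may leave slide coding and reading order to a full protocol or a pathology manual. This stands: the supportable statement is that no masking is described, not that reading is unmasked.

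The inference is still not idle. The article is specific about other measurement conditions: the hours, room and attending physician for saliva collection, the MRI diffusion settings, and the gland and side to be punctured. It sets out the histology comparison in detail without any safeguard of this kind.

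The second objection is consequence. The outcomes are secondary and descriptive in a 10-patient exploratory study, and no test on them is planned. This stands too, and it limits the severity.

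The third is that masking would not allow a change to be attributed to treatment, since there would still be no control tissue. That is correct. Masking removes one source of error and leaves the others. It might also be imperfect if the first biopsy leaves a visible trace in the same gland.

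**Conclusion.** The point holds in a limited form. The histology comparison and the pertechnetate read are judgement-based before/after assessments in an open-label study that expects benefit. They have no control tissue or images, and no masking of the reader to visit is described. The plan as written permits reader expectation to shift these results.

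The size of any shift cannot be derived from the document, and any number of percentage points put on it would have no basis there. The conclusion assumes that no masked reading procedure exists in a document not shown. If one does, a sentence saying so settles the matter.

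Two wider readings are not supported. The article does not state how much manual judgement the MRI volumetry needs, so MRI volume and diffusivity cannot be counted as subjective reads. Nor do the primary safety objective or the salivary flow analysis depend on these readings, so the trial's main conclusions are not in question. Severity is low to moderate, and the remedy is a cheap improvement.

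**What to change.** After a patient's day 120 visit, code that patient's stored slides and pertechnetate studies, together with any MRI signal changes that are judged by eye. Randomise the visit order, and have the same reader score the material masked to visit. Use these scores for the before/after comparison. Keep the immediate baseline read for clinical purposes only. State the procedure in one or two sentences in the biopsy and scintigraphy sections, or say there that it is already in place.

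The cost is small: no extra reader, procedure or patient visit. Someone other than the reader must hold the code. Research reads wait until day 120, and baseline material is read twice, which for histology means 10 additional specimen reads (one per patient).

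Elastography is outside this fix because it is measured live at the visit. MRI volume and diffusivity need no change on the evidence in the article.
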